| Tan et al described that with oral 20mg methylprednisolone monotherapy in IGM, 80.7% of patients responded well to steroid treatment. The rationale for a lower starting dose of oral prednisolone of 20mg for Asians is due to higher risk of developing side effects to steroid as compared to their Caucasian counterparts. For this study, 20 mg of prednisolone will be prescribed daily for first 2 weeks, followed by tapering doses of 15mg daily over 2 weeks, then 12.5 mg daily for 2 weeks, proceeding to 10 mg daily for 2 weeks, subsequently taking 7.5mg daily for 2 weeks and lastly 5mg daily for 2 weeks (refer to Figure 2). 20mg of omeprazole is to be taken together with prednisolone. (Refer to Section 8.6 on justification for omeprazole).  Postolva et al described that with oral methotrexate monotherapy (starting dose of 10-15mg/week and increased to 20-25mg/week given orally or subcutaneously) in IGM, 94% had disease improvement^16^. Only oral formulation of methotrexate was chosen in our study to standardize the bioavailability and ease of administration in this trial^17^. In this study, 10mg of methotrexate will be prescribed to be taken once a week for a month and increased to 15mg of methotrexate to be taken once a week for another two months. 5mg of folic acid is to be taken together with methotrexate once a week (Refer to Section 8.6 on justification for folic acid).  *Modification of doses*  Modification of doses may occur during the study period and this will be dependent on patient’s clinical response and the attending doctor’s judgement. Principal Investigator (PI) or Co-Investigators (Co-Is) may increase the methotrexate dosage from 15mg to 20mg and may increase the 5mg folic acid intake up to 6 times a week (except the day of taking methotrexate) to mitigate methotrexate’s side effect, if needed. |  |
| Rationale for Study Population |  |
| The reported incidence of IGM is around 2.4 per 100,000 women aged 20–40 years. The study team will be including women aged 21 to 60 years because IGM often affects women who are young to middle aged. In addition, any women below the age of 21 years are unable to give consent independently in Singapore. |  |
| Rationale for Study Design |  |

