| This is a prospective pilot randomised trial to study the effectiveness of prednisolone versus methotrexate in achieving clinical or radiological complete response for women with IGM. Patient will be recruited from NUH and written informed consent will be obtained prior to screening and enrolment. Patient will be randomised to one of the treatment arms.  The 2 arms consist of:   - Control arm (20 patients):   - Prednisolone tablet will start at 20mg daily for first 2 weeks (Refer to Figure 2 for tapering doses) with 20mg of omeprazole daily (Refer to Section 8.6) - Experimental arm (20 patients):   - Methotrexate tablet will start at 10mg once a week for the first month (Refer to Figure 2 for increasing of dosage) with 5mg of folic acid (Refer to Section 8.6) |  |
|  |  |
| **METHODS AND ASSESSMENTS** |  |
| Randomisation and Blinding |  |
| Permuted block randomisation will be performed with randomly varying block sizes of 4 and 6. Eligible and consented participants will then be randomly assigned to either of the treatment arm based on their baseline visit date. |  |
| Contraception and Pregnancy Testing |  |
| We do not accept women who self-report or test as pregnant during recruitment. |  |
| Study Visits and Procedures |  |
| **Study Visits and Procedures** |  |

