| Investigational Product (IP):   1. Prednisolone: 20mg/day. Y.S.P Prednisolone 5mg by Y.S.P. Industries (M) Sdn Bhd 2. Methotrexate: 15mg/week. Emthexate 2.5mg by TEVA Czech Industries S.R.O   Auxiliary Product (AP):   1. Omeprazole: 20mg/day. Zenpro Omeprazole 20mg by XEPA-SOUL Pattinson (Malaysia) Sdn Bhd 2. Folic acid: 5mg/day. Folic Acid Sunward tab 5mg by Sunward Pharmaceutical Pte Ltd |  |
| Storage and Drug Accountability |  |
| The PI and study team will be responsible to maintain the storage in IMU and drug accountability for all the trial product. | |
|  | |
| **TREATMENT** | |
| Rationale for Selection of Dose | |
| For safety reason, the dose of drugs used in this study is standard dosage in accordance with the approved labels. | |
| Study Drug Formulations | |
| All drugs dispensed to the patients are in tablet (methotrexate, folic acid, prednisolone) form and capsule form (omeprazole) for oral consumption. | |
| Study Drug Administration |  |
| 1. 20 mg of prednisolone daily for first 2 weeks, followed by tapering doses of 15mg daily over 2 weeks, then 12.5 mg daily for 2 weeks, proceeding to 10 mg daily for 2 weeks, subsequently taking 7.5mg daily for 2 weeks, and lastly 5mg daily for 2 weeks (refer to Figure 2). 20mg of omeprazole is to be taken together with prednisolone. 2. 15mg of methotrexate to be taken once a week for a month, and increased to 20mg of methotrexate to be taken once a week for another two months. 5mg of folic acid is to be taken together with methotrexate.   PI or Co-Is may increase the methotrexate dosage from 20mg to 25mg depending on patients’ responses to the drug and doctor’s discretion. PI or Co-Is may increase 5mg folic acid intake up to 6 times a week (except the day of taking methotrexate) to mitigate methotrexate’s side effects, if needed. |  |
| Specific Restrictions / Requirements |  |

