| During the course of the study, patients on both treatment arms will be instructed to/advised:   1. Not get pregnant or try to get pregnant 2. No breastfeeding 3. Avoid alcohol 4. Inform the PI/Site PI/doctor before getting any vaccinations during study period 5. Strictly refrain from concurrent dosing with other medicines, including prescriptions, and to inform the investigator(s) immediately about any new medication they need/want to take 6. Take medication as per packaging instructions   For patients on methotrexate, an additional instruction of not consuming tolbutamide and/or co-trimoxazole will be given, due to possible drug interactions. |  |
| Blinding |  |
| This is a prospective pilot open label randomised trial. Patients and study team will not be blinded with regards to the treatment assigned. |  |
| Concomitant therapy |  |
| 20mg/day of omeprazole tablet will be taken with prednisolone tablet to reduce the irritation to the stomach caused by prednisolone.  5mg of folic acid tablet will be taken with methotrexate tablet every week to reduce bone marrow suppression. |  |
| **SAFETY MEASUREMENTS** |  |
| Definitions |  |
| Prednisolone and methotrexate have been widely used in local clinics for various diseases.    Prednisolone can be used to help reduce inflammation and reduce symptoms of swelling, redness and itchiness. It has been widely used to treat various diseases such as asthma, allergic conditions, skin problems, etc. It is also the standard of care treatment given to IGM patients in NUH and has a good safety profile.  Methotrexate is commonly used by rheumatologists for treatment of autoimmune diseases such as rheumatoid arthritis, systemic lupus erythematosus (SLE), etc.  Adverse events will be reported according to Common Terminology Criteria for Adverse Events (CTCAE) Version 5.0. |  |
| Collecting, Recording and Reporting of “Unanticipated Problems Involving Risk to Subjects or Others” – UPIRTSO events to the NHG Domain Specific Review Boards (DSRB) |  |

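### Sections 1.2a and 5.1 give one methotrexate schedule and Section 8.3 a higher one, so the experimental regimen is not uniquely defined

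*Protocol*

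**What the plan says.** **Methotrexate.** Three places fix a dose by time.

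- Section 1.2a, Rationale for Doses Selected: "10mg of methotrexate will be prescribed to be taken once a week for a month and increased to 15mg of methotrexate", the second dose being for two months. Under the dose-modification paragraph, investigators "may increase the methotrexate dosage from 15mg to 20mg".
- Section 5.1, Summary of Study Design: "Methotrexate tablet will start at 10mg once a week for the first month". For the later increase it refers to Figure 2, which is not reproduced in the text at hand.
- Section 8.3, Study Drug Administration: "15mg of methotrexate to be taken once a week for a month, and increased to 20mg of methotrexate to be taken once a week", the second dose again being for two months. Investigators "may increase the methotrexate dosage from 20mg to 25mg".

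The Section 7.1 product list carries a single methotrexate figure of 15 mg per week, supplied as 2.5 mg tablets.

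**Folic acid.** Section 1.2a has 5 mg once a week with methotrexate. Section 8.6 agrees: "5mg of folic acid tablet will be taken with methotrexate tablet every week". Section 8.3 has it taken with methotrexate, which is weekly by implication. The Section 7.1 product list has "Folic acid: 5mg/day". Sections 1.2a and 8.3 share an optional increase to as many as six times a week, leaving out the methotrexate day.

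**Prednisolone.** The taper is the same in Sections 1.2a and 8.3, so the conflict affects the experimental arm only.

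**The concern.** Sections 1.2a and 8.3 are both written as the instruction for this study, and neither yields to the other. A clinician or pharmacist working from 8.3 would start and step up at doses 5 mg per week higher than a colleague working from 1.2a or 5.1.

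Three things are at stake.

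- **Safety.** Section 9.4 names lowered blood counts and liver inflammation as methotrexate risks, and Section 8.6 gives folic acid to limit marrow suppression. Section 8.4 tells patients to follow the packaging, so a label drawn from one section would conflict with another. Section 9.4 also makes further blood tests follow from a dose increase required by the doctor. A dose of 20 mg is such an increase under 1.2a, but the routine dose from the second month under 8.3.
- **Interpretation.** The hypothesis is about both response and side effects. With 20 patients planned for methotrexate, an unplanned mixture of two schedules would leave it unclear which regimen produced either result.
- **Adherence and deviations.** Leftover medication is counted to check adherence, and the per-protocol analysis refers to a completed regimen. Both need a single reference schedule. Re-treatment after relapse goes back to the allocated arm and so carries the same ambiguity.

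**Working it through.** The protocol gives no cumulative dose to reproduce. The check sets the sections side by side and then sizes the gap.

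| Item | Section 1.2a | Section 5.1 | Section 8.3 |
|---|---|---|---|
| Month 1, mg/week | 10 | 10 | 15 |
| Months 2 and 3, mg/week | 15 | see Figure 2 | 20 |
| Stated optional increase, mg/week | 15 to 20 | not given | 20 to 25 |

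**Cumulative scheduled methotrexate** = (month 1 dose × weeks in month 1) + (later dose × weeks in months 2 and 3).

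Assuming a four-week month, so 4 + 8 = 12 weeks (the six two-week prednisolone steps also give 12 weeks):

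- Section 1.2a: 10 × 4 + 15 × 8 = 40 + 120 = 160 mg, a mean of 160/12 = 13.3 mg/week.
- Section 8.3: 15 × 4 + 20 × 8 = 60 + 160 = 220 mg, a mean of 220/12 = 18.3 mg/week.
- Difference 60 mg; ratio 220/160 = 1.375, that is +37.5%.

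With calendar months of 52/12 weeks:

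- Section 1.2a: 10 × 4.333 + 15 × 8.667 = 173 mg.
- Section 8.3: 15 × 4.333 + 20 × 8.667 = 238 mg.
- The ratio is again 1.375, so the relative gap does not depend on how a month is counted.

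**Tablet count.** With 2.5 mg tablets, the 12-week totals are 160/2.5 = 64 and 220/2.5 = 88 tablets. A patient who took 64 tablets would be fully adherent under 1.2a and at 64/88 = 73% under 8.3.

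**Does titration explain the gap?** No. Each version allows discretionary increases on top of its fixed doses, and it is the fixed doses that differ.

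**Does Section 7.1 settle it?** No. Its 15 mg/week is the later dose in one version and the starting dose in the other.

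**Folic acid.** Weekly: 5 × 1 = 5 mg/week. Section 7.1 read as a schedule: 5 × 7 = 35 mg/week. Optional increase at six times a week: 5 × 6 = 30 mg/week. Read as a schedule, the 7.1 entry would therefore exceed the optional increase.

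**The case against.** Several points limit how far this can be pressed.

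- **A reader might infer that the treatment comparison becomes uninterpretable.** The protocol does not support that. The trial is an open-label randomised pilot with an intention-to-treat primary analysis. Both versions allow discretionary increases, and Section 6.3 has doctors up-titrate at flares and possibly at month 6, so some spread of doses within the arm is planned. The randomised arms can still be compared. The double schedule adds variation that nobody planned and leaves the tested regimen unclear.
- **A reader might infer that per-protocol status and adherence cannot be judged.** Section 11.2 defines the per-protocol group by completing six months of treatment and names no dose, and returned medication can be counted against what was dispensed. What is lost is a single standard for what the regimen is and what deviates from it.
- **A reader might infer a sevenfold conflict in scheduled folic acid.** Only the product list differs. That list gives one reference figure per product: prednisolone appears there at its starting dose although it is tapered. The 35 mg/week figure holds only if the entry is read as a schedule.
- **A reader might speak of two permitted maxima.** Neither optional increase is called a maximum, and the up-titration in Section 6.3 names no ceiling.
- **Safeguards exist.** Blood counts and liver and renal tests are due at months 1, 2, 3 and 6, rheumatologists oversee side effects and titration, and a data monitoring committee reviews adverse events. These reduce the risk but do not tell anyone which schedule to follow.
- **Figure 2 is not visible here.** It may match one version, but it cannot make the written sections agree with each other. Nor does the reference to approved labels in Section 8.1 choose between them.

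These points narrow the consequences. None removes the contradiction in the fixed methotrexate doses.

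**Conclusion.** This is an internal inconsistency, wrong as written, and should be corrected before anyone is dosed from the document. The starting dose differs by 5 mg/week (10 v 15), the step-up dose by 5 mg/week (15 v 20), and the endpoint of the optional increase by 5 mg/week (20 v 25). The scheduled total differs by 37.5%: 160 v 220 mg over 12 weeks, or 173 v 238 mg with calendar months. The totals assume that every weekly dose is taken and no discretionary change is made.

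That patients could be treated under either version is a fair inference from two competing instructions. The protocol gives no evidence that it has happened. If one version has been used throughout, the harm is a misdescribed regimen; if both have been used, the experimental arm mixes two schedules. The folic acid discrepancy is secondary and comes from the product list alone. No view is taken here on which dose is right.

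**What to change.** The investigators should:

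1. Reconcile Sections 1.2a, 5.1, 7.1, 8.3, 8.6 and Figure 2 to one methotrexate schedule, one optional-increase rule and one folic acid schedule, all of their choosing.
2. State these once, in Section 8.3, and replace the figures elsewhere with cross-references.
3. Make the Section 7.1 entries either match that schedule or be marked clearly as product reference figures. Also make plain how the optional folic acid increase, which leaves out the methotrexate day, fits with a base dose taken together with methotrexate.
4. Check pharmacy labels and order sets against the reconciled text.
5. For any patient already treated, record which version she received, so that response, side effects and deviations can be described by the schedule actually given.

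The cost is one protocol amendment with ethics review and a check of labels and order sets. It needs no extra patients, visits or procedures.

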| This is a prospective pilot randomised trial to study the effectiveness of prednisolone versus methotrexate in achieving clinical or radiological complete response for women with IGM. The study will be conducted in NUH. This study evaluates the effectiveness of each drug in terms of clinical and/or radiological response, time to resolution as well as total number of flares over a period of one year follow-up. This study can potentially identify a more effective treatment with fewer side effects for women with IGM as well as personalize drug choices for patients who are at risk of frequent flares. |  |
| **HYPOTHESIS AND OBJECTIVES** |  |
| Hypothesis |  |
| The hypothesis is that methotrexate has a higher 6-month clinical or radiologically complete response with lesser side effects than prednisolone. The time to clinical or radiological response is shorter in the methotrexate arm compared to prednisolone arm. Relapse and time to first relapse is lower and longer in the methotrexate arm compared to prednisolone arm. |  |
| Primary Objectives |  |
| The primary objective is to evaluate the 1) Proportion of patients who achieved clinical or radiological complete response at 6 months 2) Time to clinical response and time to radiological response, and 3) Proportion of patients with relapse in one year within affected breast between each arm. |  |
| Secondary Objectives |  |
| The secondary objectives include evaluation of:   1. Side effects 2. Frequency of percutaneous or surgical intervention required 3. Potential biomarkers that may predict response to treatment: eg IL-6, CRP and neutrophil to lymphocyte ratio (NLR) 4. Patient reported outcome measures 5. Validate survey instrument for IGM patients |  |
| Potential Risks and benefits |  |
| End Points – Efficacy |  |
| Benefits expected for the patient are the total remission of IGM or reduced relapsed/flare of IGM. |  |
| End Points – Safety |  |

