| *Screening*  After patient is consented to the study, a baseline blood test (32mls, including pregnancy test, Hepatitis B test, Hepatitis C test, full blood count, liver function test and renal function test) and chest X-Ray will be conducted during the baseline visit to assess for eligibility prior to enrolment to the treatment phase. Additional research blood (14.5mls, 1 tablespoons) will be collected at this baseline visit for research purposes. Patient may be exempted from chest X-Ray and/or blood test if patient has done the same test within 30 days.  Baseline demographics and relevant clinical variables of patients will be collected. The following demographic and clinical variables will be collected: age of presentation, pre-menopausal or post-menopausal status, parity / breastfeeding status, concomitant rheumatic conditions, personal or family history of tuberculosis, smoking or alcohol intake, presenting complaint, unilateral or bilateral involvement, affected quadrant of the breast, duration of symptoms and previous antibiotics prescription for treatment of IGM.  Information on comorbidities will be evaluated to ensure suitability for both treatment arms prior to recruitment. Examples include drug allergies, plans for pregnancy, ongoing infection, previous history of cancer, previous tuberculosis, epilepsy, diabetes, hypertension, kidney, liver, cardiac problems, osteoporosis, glaucoma, peptic ulcers, previous side effects to either prednisolone or methotrexate.  If patient fulfilled all the eligibility criteria after screening assessment, she will be randomised to either of the treatment arm.  If patient did not meet the full eligibility criteria (eg. Pregnant, hepatitis carrier or abnormalities in renal or liver panels), she will not proceed to the treatment phase. The data collected and additional blood samples will be kept for analysis.  *Treatment Phase*  Patient will be scheduled to attend a clinical visit (T_0_) to either breast or rheumatology clinic if she meets all eligibility criteria for the initiation of treatment dose. There will be a window period of ± 7 days for this clinical visit. Patient is required to complete a pre-treatment quality of life online survey (approximately 10-15 minutes).  Patient will be scheduled for blood test (8mls, 0.5 tablespoons) and clinical visits to either breast or rheumatology clinic at the 1^st^ (T_1_), 2^nd^ (T_2_), 3^rd^ (T_3_) and 6^th^ (T_4_) month to assess their signs and symptoms, and drug compliance. There will be a window period of ± 14 days for each of these clinical visits. Additional research blood (14.5mls, 1 tablespoons) will be collected on the 1^st^ (T_1_) and 6^th^ (T_4_) months.  Patients are required to undergo a breast ultrasound to assess for their radiological response during the 3^rd^ (T_3_) clinical visit. A window period of ± 14 days will be applicable. The initial measurement of the breast lesion or mass will be recorded in three dimensions – i.e. anteroposterior, superior-inferior, mediolateral measurements. If complete clinical and radiological complete response has been achieved on the 3^rd^ (T_3_) visit, the doctor will discontinue the drug in a safe manner and no further breast ultrasounds will be required. If the patient’s symptoms or signs have not resolved by the 3^rd^ (T_3_) clinical visit, patient’s drug dosage will be assessed by the rheumatologist and treatment may be continued up to the 6^th^ (T_4_) month period and a repeat breast ultrasound will be required at the 6^th^ (T_4_) month. If symptoms have not resolved by the 6^th^ (T_4_) month of clinical visit, the patient’s drug dosage may be up-titrated or will be given an addition of a second therapy, i.e. combination therapy of steroid and methotrexate may be used. For clinical visits mention above, it will coincides with standard care visit.  During the clinical visits, Tingting Hu et al’s “M- score” will be adopted to grade the severity of the disease. M score is being calculated during clinical visits for IGM patients regardless of trial status for objective follow up. This is a common practice. For this study, the score will be administered by their attending healthcare professional (not limited to breast surgeons, investigators, or breast care nurses).  The M-score will be the sum of the following:  1) Mass score  2) Erythema score  3) Fistula score  4) Pain score  5) Quality-of-life (QoL) score  The scoring criteria were defined as follows:  1) Mass score: 0 for the absence of mass by palpation; 1 for mass ≤3 cm by palpation; 2 for mass >3 cm by palpation.  2) Erythema score: 0 and 2 for the absence and presence of erythema, respectively  3) Fistula: 0 and 2 for the absence and presence of fistula, respectively  4) Pain Score: 0 for Visual Analogue Score (VAS) 0-2; 1 for VAS 3-5; 2 for VAS 6-10  5) QoL score: 0 for absence of effects on QoL; 1 for mild effects on QoL, where the patient does not require medical assistant; 2 for serious effects on QoL, where the patient requires medical assistant  The total M-score ranges between 0 and 10 and serves as a quantitative and objective measurement of the severity of the symptoms.  The primary endpoint will be the clinical complete response (cCR) rate, which is defined as the proportion of patients who have an M-score of ≤ 1 at ≤1 years after treatment.  The secondary endpoints will be as follows:   - - The time to cCR, defined as the median time to cCR post randomisation.   - The treatment failure (TF) rate, defined as the proportion of patients with TF at 1 year post randomisation. The TF status will be defined as follows:     - If the patient has an M-score ≥6 before randomisation, TF is defined as the M-score remaining at ≥6 at 1 month post randomisation.     - If the patient has an M-score between 4 and 5 before randomisation, TF is defined as the M-score remaining at ≥4 and never being lower than 4.     - If the patient has an M-score <4 at baseline but never reaches cCR after randomisation, TF is defined as the M-score being >5 at the follow-up and remaining above 5 for one month. - Relapse rate, which is defined as the proportion of patients who have M-score >4 among the patients who achieved CR.   Throughout the course of the study, there are possible flares and relapse of the disease. Flares will be defined as any increase in M-score or lesion size on ultrasound whilst on therapy. While relapse will be defined as recurrence of symptoms or signs of IGM in the breast after previously experiencing complete resolution following therapy. If relapse occurs, patient will restart the same treatment arm for 6 months.  In the event of flares, blood test (8mls, 0.5 tablespoons) and additional research blood (14.5mls, 1 tablespoons) will be collected and the allocated treatment for the patient will be up-titrated by the doctor. In event of relapse, treatment for the patient will be reinitiated as per the allocated arm.  Additional research blood samples collected during the trial will be used for gene expressing profiling to identify unique patterns of gene expression that can be used to diagnose IGM and predict its treatment response.  Regardless of treatment arm, patient will be monitored by either breast surgeon or rheumatologist. Surgeons will assess for eligibility into trial, clinical reviews, and ultrasound breasts interpretation. Rheumatologists will be monitoring for drug side effects and titration if required. In event of failure of medical therapy, surgeons will have to intervene accordingly for aspiration or surgical drainage. In the event where patients require aspiration or surgical drainage during the study, methotrexate or prednisolone should be continued unless there is evidence of sepsis. The frequency of aspiration or surgical intervention will be recorded as events during the study.  Whenever the disease has been resolved during the study period, the balance medication and/or packaging will be retrieved to do medication accounting and checking for adherence to assigned treatment arm.  If side effects were to develop, doctors will evaluate the severity of the side effects and withdraw the patients from the trial if needed. |  |

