| De-identified blood samples will be analysed and stored in NUH Tissue Repository. Recruitment and follow-up survey data will be collected electronically via NUHS REDCap. Only study team members with delegated rights will be able to access the data under the supervision of PI and Site-PI. All survey data will be collected electronically via FormSG. A copy of de-identified data will be stored in a secured server at NUH. |  |
|  |  |
| **SAMPLE SIZE AND STATISTICAL METHODS** |  |
| Determination of Sample Size |  |
| The prevalence rate of IGM in NUH is currently at 10 to 15 patients per year. Based on a stepped rule of thumb, a minimum sample size of 30 will provide at least 80% power to detect a medium standardised effect size of between 0.3 to 0.7 based on a randomised two-group comparison (Machin et al, 2021). Assuming a 20% attrition rate, the sample size required for this study is 36 patients. This will be rounded up to a sample size of 40 patients over a period of 36 months. |  |
| Statistical and Analytical Plans The primary outcome of 6-month clinical or radiological complete response will be compared between arms using Chi-square test. The effect estimate will be quantified in terms of difference in proportion as well as relative risk (RR) and their associated 95% confidence interval (CI). The secondary outcomes of time-to clinical or radiological response and time-to-relapse will be evaluated via the Kaplan-Meier method. The differences in survival curves will be compared using log rank test, with the effect estimate quantified in terms of hazard ratio and its 95% CI. The primary analysis of this trial will be based on Intention-to- Treat (ITT). A Per Protocol (PP) analysis will be performed on all patients who have completed 6 months of treatment regimen as a sensitivity analysis.  Chi square test will be used to evaluate the proportion of side effects and requirement for percutaneous or surgical intervention during treatment between arms. Modified Poisson regression will be used to identify clinical or biomarkers that are associated with treatment response and quantify the effect in terms of RR.  Patient reported outcomes will be reported via a survey on FormSG, conducted online. The questions will be adapted from SF36 V1 Singapore version and EORTC-BR23. Below are the domains to be compared:   - - General Health   - Physical Health   - Mental Health   - Body Image   - Sexual Image   - Breast Health |  |
| **ETHICAL CONSIDERATIONS** |  |

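### Nothing in Sections 8.5 and 6.3 keeps the ultrasound reader unaware of the arm, although a complete response on ultrasound alone can make a patient a responder under Sections 2.2 and 11.2

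*Protocol*

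**What the plan says.** Section 8.5 describes an open-label trial: "Patients and study team will not be blinded with regards to the treatment assigned". It makes no exception for whoever assesses outcomes. Section 6.1 is headed Randomisation and Blinding but describes only the randomisation.

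Section 6.3 assigns the imaging task to the surgeons as a group: "Surgeons will assess for eligibility into trial, clinical reviews, and ultrasound breasts interpretation". On the scans themselves it says:

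- Month 3: "Patients are required to undergo a breast ultrasound to assess for their radiological response during the 3^rd^ (T_3_) clinical visit".
- Month 6, if symptoms or signs have not resolved by month 3: "a repeat breast ultrasound will be required at the 6^th^ (T_4_) month". Figure 1 marks the month-6 scan as being at the doctor's discretion.
- Measurement: "The initial measurement of the breast lesion or mass will be recorded in three dimensions".

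The result feeds the main comparison. Section 2.2 lists "Proportion of patients who achieved clinical or radiological complete response at 6 months" as the first primary objective, with time to radiological response as part of the second. Section 11.2 states: "The primary outcome of 6-month clinical or radiological complete response will be compared between arms using Chi-square test". Section 6.3, however, also says "The primary endpoint will be the clinical complete response (cCR) rate" and defines that rate by the M-score alone.

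**The concern.** The dosing schedules differ visibly, and running the trial open label is a reasonable choice. The difficulty is narrower: the absence of blinding extends to the reading of the scans, where it is not needed. The M-score requires contact with a patient who knows her treatment. An ultrasound can be interpreted by someone who has not been told the arm.

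Three features leave room for expectation to act on the reading. The protocol gives no criterion separating a residual lesion from a radiological complete response. The hypothesis in Section 2.1 is directional and favours methotrexate. The outcome in Sections 2.2 and 11.2 is an either/or composite, so a scan read as complete turns a clinical non-responder into a responder.

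If borderline scans are read more favourably in one arm, a difference can be created or hidden in the 6-month outcome and in time to radiological response. The intention-to-treat and per-protocol analyses use the same readings, so neither can correct this. A later analysis plan cannot mask a scan that has already been read unmasked.

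**Working it through.** **Textual check.** The protocol gives no figure for this point, so the first step is to set the sections side by side.

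1. Section 8.5: the study team is unblinded, without exception.
2. Section 6.3: the surgeons are the readers and also do clinical reviews.
3. Sections 2.2 and 11.2: radiological complete response alone is enough for success at 6 months.
4. No section provides a masked, independent or central reader, or says why one would be impracticable.

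From 1 to 4, an arm-aware reading of the radiological component is permitted and nothing guards against it.

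**Illustration of size.** Input from the protocol: 20 patients per arm (Section 5.1) and a chi-square test (Section 11.2). Assumed, not in the protocol: a two-sided 5% level without continuity correction; equal true response p of 60% or 70% in both arms; and an expected k net false complete readings in one arm only, all in patients who are not clinical responders. The observed response probability in that arm is then p + k/20.

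With X ~ Bin(20, p) and Y ~ Bin(20, p + k/20), the rejection probability is the sum of P(X = x)·P(Y = y) over all pairs where |x − y|/20 ÷ √(p̄(1 − p̄)·2/20) > 1.96, with p̄ = (x + y)/40.

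| k | Added points | p = 60% | p = 70% |
|---|---|---|---|
| 0 | 0 | 4.8% | 5.3% |
| 1 | 5 | 6.3% | 6.7% |
| 2 | 10 | 10.4% | 11.4% |
| 3 | 15 | 17.9% | 20.5% |

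**How demanding is each k?** At 60% response an arm has 20 × 0.40 = 8 expected non-responders, so k = 1, 2, 3 means misreading 12.5%, 25% or 37.5% of them. At 70% there are 20 × 0.30 = 6, so the shares are 17%, 33% or 50%.

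**Second bias model.** Suppose instead that a share f of non-responders in one arm is read as responders. The spurious difference is f × (1 − p).

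| p | f = 0 | f = 20% | f = 30% |
|---|---|---|---|
| 50% | 4.3% | 8.7% | 15.0% |
| 60% | 4.8% | 8.4% | 13.0% |
| 75% | 5.1% | 6.7% | 8.8% |

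The direction is the same. The inflation is smaller when response is high, because fewer patients are left to be misclassified.

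**The case against.** The strongest reply is that Sections 8.5 and 6.3 are consistent with each other: the protocol declares an open-label, single-centre pilot of 40 patients and does not claim masked assessment. That stands. This is an avoidable weakness in the design, not an error or contradiction in the blinding text.

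Four further points limit how far the concern reaches.

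- **Which primary endpoint.** Under the M-score definition in Section 6.3, ultrasound plays no part in the primary endpoint. The effect on the primary outcome therefore depends on how that conflict is resolved. Time to radiological response is affected either way; Section 2.2 places it among the primary objectives and Section 11.2 treats time to clinical or radiological response as secondary.
- **What the reader knows.** A reader might infer that each surgeon interprets her own patients' scans knowing the dose and the M-score. The text does not say so. It names surgeons collectively, follow-up is by a breast surgeon or a rheumatologist, titration belongs to rheumatologists, and the M-score may be recorded by nurses or others. Section 8.5 supports only that the arm is not concealed.
- **Overlap.** A false complete reading in a patient who is already a clinical responder leaves the composite unchanged. Two or three net changes are a demanding assumption; one gives only a small inflation.
- **Partial remedy.** The M-score, with its pain and quality-of-life items, remains unmasked and is enough for success. At a centre seeing 10 to 15 patients a year, a colleague may know the arm anyway. The protocol does not state how many surgeons there are or whether images are stored for later reading.

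None of this removes the gap. The radiological component can be protected, the protocol leaves it unprotected, and calling the trial a pilot does not settle the matter, because Section 11.2 plans a formal comparison with effect estimates and confidence intervals.

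**Conclusion.** The point holds in limited form. The protocol allows the radiological component of the 6-month outcome in Sections 2.2 and 11.2, and time to radiological response, to be read in knowledge of the arm. It provides no safeguard and gives no reason for omitting one.

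The actual size is unknown. With one to three net one-sided misreadings among clinical non-responders, the false-positive rate would be about 6% to 18% at 60% response and 7% to 20% at 70%, against roughly 5% without bias. These figures rest on the assumed number of misreadings, on all of them falling in one arm, and on none falling in a clinical responder.

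The documents do not support saying that the readings will be biased, that open-label treatment is itself a fault, or that masked reading would make the composite free of detection bias. The change is worth making because it is cheap.

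**What to change.** - **Section 8.5:** limit the statement on absence of blinding to patients and treating staff.
- **Section 6.3:** state that, for the outcome of record, the planned month-3 ultrasound and any month-6 ultrasound are interpreted by one of the existing study surgeons who is not following that patient, with arm, dose and M-score withheld from the request. This reading replaces the planned one; it is not a second reading.
- **Sections 6.3 and 11.2:** state that the M-score is still scored unmasked, so the change reduces but does not remove detection bias.
- **Sections 2.2, 6.3 and 11.2:** reconcile the composite with the M-score-only primary endpoint, so that it is clear whether the ultrasound contributes to the primary outcome.

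The cost is protocol wording and some allocation of readings among the surgeons, for at most 40 × 2 = 80 planned scans and fewer where the month-6 scan is not done. No scan or reading is added. That no additional reader is needed assumes more than one surgeon is available, which the plural in Section 6.3 suggests but does not quantify.

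The drawbacks are less clinical context for the reader, a possibly slightly later report, and masking that may be imperfect at a single centre. Timing needs attention because the month-3 result also informs the decision on continuing treatment in Section 6.3.
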